### Additional treatment

Patients can receive full supportive care during and after the administration of ICIs. Palliative radiotherapy, surgery, corticosteroids/other immunosuppressive agents, transfusion with blood products and bisphosphonates are all allowed.

### Treatment for disease progression or relapse

Treatment for disease progression in the metastatic setting and for relapse on or after adjuvant therapy is at the Investigator’s discretion and local practice. Patients deriving clinical benefit from palliative therapy with ICIs in the presence of progression determined by RECIST 1.1 may continue on treatment beyond progression at the investigator’s discretion. However, no further formal RECIST reporting will be required.

For patients with advanced disease, the first RECIST progression date will be used for measuring PFS in this study. For adjuvant patients, the first date of relapse will be used for measuring RFS.

### Collection of clinical data

No additional clinic visits or consultations are required for this study over and above standard of care. Cancer patients will be followed up during their routine clinic visits/consultations, with study data collection time points approximating to baseline (pre-treatment), 6–8 weeks, 12 weeks, 3 monthly up to 1 year, then 6 monthly thereafter until disease progression or relapse, up until the study closure date. Additional clinic assessments may be required as per local practice but study data collection will only be required if the assessment is for first disease progression/relapse. Details of data collected at each visit is available in Additional file 3.

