**Fig. 1 Fig1:**
[figure not shown]
MITRE Study Flow Chart

Cancer patients due to commence standard treatment with systemic therapy including an anti- PD- (L)1 ± anti-CTLA-4 antibody will be invited to take part in this multi-cohort, multi-centre study.

Consenting patients will be asked to provide clinical information and donate biological samples before, during and after completing their treatment (see section Additional file 1), for the duration of the study period, up to a maximum of 5 years.

Consenting patients will also be asked to invite a member of their household to provide limited demographic, health and lifestyle information and biological samples at a single time point only (see Additional file 2).

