#### Secondary outcome measures

The ability of the microbiome signature to predict 6 month PFS, 2 year PFS, overall response rate, median PFS and median overall survival (OS) in cohorts 1–6.The ability of the microbiome signature to predict for 1 and 2 year relapse after resection of high risk melanoma or renal cancer in cohorts 7–9. (Table 2 and Fig. 2)

**Table 2 Tab2:** Cohorts 7–9 – Adjuvant disease cohorts and defined standard of care ICI-containing treatment regimens

Cohort	Disease	Regimen	Primary outcome measure
Cohort 7	Resected AJCC stage 3 or 4 melanoma	Anti-PD-1 monotherapy (nivolumab or pembrolizumab)	1 year & 2 year RFS
Cohort 8	Resected renal cancer	Durvalumab	1 year & 2 year RFS
Cohort 9	Resected renal cancer	Durvalumab+tremelimumab	1 year & 2 year RFS

To compare oral and gut microbiome findings and their association with treatment efficacy.To correlate microbiome findings with incidence and characteristics of CTCAE V5-defined Grade > 3 IrAEs in all enrolled patients, and any association with response to immunosuppressants.To correlate microbiome findings with aspects of pre-existing patient characteristics and behaviour including but not limited to diet, smoking history, BMI, use of antibiotics, steroids, PPIs, NSAIDs and probiotics.To compare the microbiome signature of cancer patients with a household control group of people who are not known to have cancer.To retain a library of biological samples with linked patient data for future research.

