### Assessments on study

Patients will be followed up during their routine clinic visits, with study-specific data collection at time points approximating to baseline (pre-treatment), 6–8 weeks, 12 weeks, 3 monthly until 1 year, then 6 monthly thereafter until and including disease progression, or relapse, or study termination.

Immune-related adverse events (IrAEs) will be recorded at each clinic visit.

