### ICI treatment

Specific details of the systemic therapy regimens being used to treat patients taking part in this study are not mandated in this protocol, since this is an observational study. However, all drugs (anti-cancer drugs) as well as any radiotherapy and surgery used to treat cancer during the study period will be recorded in the CRF.

Patients experiencing adverse events while on treatment are managed according to local guidelines. No routine adverse event reporting is being undertaken as part of this protocol.

Documentation of a possible/probable/definite IrAE of CTCAE grade > 3 will trigger the requirement to collect a stool and blood sample within 2 weeks of documentation (Additional file 1).

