### Statistical analysis methods

The main clinical outcome to be correlated with the gut microbiome metagenomic data will be PFS in patients with advanced disease. The hypothesis to be tested is concerned with the effect of the microbiome profile on PFS. There will be an interim analysis evaluating the effect of the biomarkers on 6-month PFS while the main analysis will assess the effect on 1 year PFS.

All primary analyses will be based upon a regularised logistic regression with the false discovery rate being controlled at 0.05 and the regularisation parameter being estimated using cross-validation.

Two sensitivity/exploratory analyses will be conducted to assess the robustness of the composition of the microbiome signature and its exact effect on the clinical outcome. The first will estimate the effect of the biomarkers on the complete survival curve (up to the particular follow-up) using a Cox model. The second will use a random forest classifier to evaluate the effect of the microbiome profile on the PFS.

Regularised logistic regression will be also used for associating the gut microbiome with a number of secondary endpoints, such as the incidence of adverse events. The secondary outcomes which depend upon the complete survival curve such the median PFS and the median OS will be correlated to the microbiome signature using a Cox model.

The logistic regression and Cox model-based analyses are likely to be conducted in R using the glmnet package. The random forest classifier will likely be fitted using the random Forest R package. A detailed statistical analysis plan will be produced before the final data base lock or before any interim analysis is performed (as appropriate).

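### Scheduled data collection ends at first progression or relapse, which does not support the secondary overall survival outcome in cohorts 1–6 and conflicts with other sections of the article

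*Protocol article*

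**What the plan says.** Two sections of the protocol article set the end of scheduled data collection, and both tie it to progression or relapse.

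- Collection of clinical data: after the first year, data points run "then 6 monthly thereafter until disease progression or relapse, up until the study closure date". For additional clinic assessments under local practice, "study data collection will only be required if the assessment is for first disease progression/relapse".
- Assessments on study: data points run "then 6 monthly thereafter until and including disease progression, or relapse, or study termination".

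Two sections make OS an outcome.

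- Secondary outcome measures: the signature's ability to predict, among others, "overall response rate, median PFS and median overall survival (OS) in cohorts 1–6".
- Statistical analysis methods: "the median PFS and the median OS will be correlated to the microbiome signature using a Cox model".

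Two sections point to collection over a longer period.

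- Study design (text below Fig. 1): patients give clinical information and samples before, during and after treatment, "for the duration of the study period, up to a maximum of 5 years".
- ICI treatment: anti-cancer drugs, radiotherapy and surgery "used to treat cancer during the study period will be recorded in the CRF".

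No section shown describes survival follow-up after progression, and none gives a censoring rule for OS. Collection of clinical data refers to Additional file 3 for the data collected at each visit; that file is not shown.

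**The concern.** OS needs a date of death, or a date last known alive, for every patient, including those who have progressed. In advanced cancer many deaths follow progression. A schedule that ends at first progression does not supply those dates, and the two sections that set the schedule make no exception for vital status.

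If nothing else fills the gap, a patient's OS time ends at progression. Progression is strongly related to the risk of death, so this censoring is informative. The Cox model for OS would then mainly describe death without progression. The study's own hypothesis adds a second problem: if the signature predicts PFS, the time of censoring depends on the signature, so its estimated association with OS would be biased. A later analysis plan can choose a censoring rule, but it cannot supply dates that were not collected.

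**Working it through.** **Sections side by side.** Collection of clinical data and Assessments on study stop the schedule at first progression or relapse. Study design and ICI treatment speak of the whole study period without that stop. Secondary outcome measures and Statistical analysis methods need follow-up for death beyond progression. The article does not say which statement governs vital status.

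**No plan figure to reproduce.** The article gives no OS event count, OS power or OS follow-up time. Table 3 concerns 1-year PFS only. What follows shows what could happen if nothing is captured after progression.

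**Inputs**

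- 12-month PFS, S₁₂: 42% and 50% for the two melanoma cohorts and 47% for NSCLC (Sample size section).
- Share q of first PFS events that are deaths: 20%. This is an assumption, varied over 10–30%.
- Median survival after progression, m: 10 months. This is an assumption, varied over 6–14 months.
- Constant hazards: an assumption.

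**Formulas** (time in months)

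- PFS hazard: λ = −ln(S₁₂)/12
- Hazard of progression while alive: λₚ = (1 − q)λ
- Hazard of death after progression: μ = ln 2/m
- OS with full follow-up: OS(t) = exp(−λt) + λₚ[exp(−λt) − exp(−μt)]/(μ − λ)
- OS if censored at progression: exp(−qλt), with median ln 2/(qλ)

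**Results at q = 0.2, m = 10** (μ = 0.6931/10 = 0.06931)

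- S₁₂ = 0.42: λ = 0.8675/12 = 0.07229. OS(20.7) = 0.50, so the full-follow-up median is 20.7 months. Censored at progression: 0.6931/(0.2 × 0.07229) = 47.9 months.
- S₁₂ = 0.50: λ = 0.6931/12 = 0.05776 and λₚ = 0.04621. OS(23.6) = 0.2558 + 0.04621 × (0.2558 − 0.1948)/(0.06931 − 0.05776) = 0.50, so the full-follow-up median is 23.6 months. Censored at progression: 0.6931/(0.2 × 0.05776) = 60.0 months.

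Over q = 10–30% and m = 6–14 months, the full-follow-up median is 16–29 months and the median under censoring at progression is 32–120 months.

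**How many deaths follow progression.** With the same model over wider assumed ranges (q = 5–30%, m = 6–24 months), deaths after progression make up these shares of all deaths:

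| By | Share of deaths that follow progression |
|---|---|
| 1 year | 29–91% |
| 2 years | 44–94% |
| 5 years | 62–95% |

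**A fixed-time view.** With S₁₂ = 0.47, q = 10% and m = 12 months, 2-year OS is 54% with full follow-up. Censored at progression it is exp(−0.1 × 0.0629 × 24) = 86%.

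**The case against.** A reader might infer that most deaths will never be recorded, or that the plan censors OS at progression. The article says neither.

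- **No censoring rule.** None is written for OS, and such a rule is commonly left to the statistical analysis plan, which the article promises.
- **Contrary text.** Study design and ICI treatment point to some collection through the study period. The treatment record suggests CRF entries after progression, though it does not show that deaths are captured.
- **Documents not shown.** Additional file 3 or the full protocol may contain a survival form.
- **Unscheduled visits.** The sentence limiting extra data collection to first progression or relapse concerns additional clinic assessments. It does not address vital status and should not be read as forbidding its collection.
- **Conditional arithmetic.** The medians need two inputs absent from the article, constant hazards and no capture at all after progression. A censored median of 60 months or more lies at or beyond the 5-year maximum and would in practice be reported as not reached. The claim that most deaths follow progression holds across the assumed range at 5 years, but not at 1 or 2 years. The bias in the Cox hazard ratio for the signature has not been quantified.

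All of this stands, and it limits the wording and the severity. It does not remove the defect. The article is not merely silent: it states a stopping point twice, and that stopping point does not fit a named outcome. If a survival form exists elsewhere, these two sections misdescribe the follow-up and still need correcting.

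**Conclusion.** The point holds in limited form. The two scheduling sections end data collection at first progression or relapse; this does not support OS in cohorts 1–6 and conflicts with Study design and ICI treatment. The consequence is conditional: if the stopping point is applied as written, the schedule misses deaths after progression and OS is in effect informatively censored there. The illustrative size, an apparent median of about 48–60 months against 21–24 months, is a hypothetical worst case resting on the assumed inputs above; it does not predict what the study will report.

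The primary outcome (1-year PFS), the 6-month PFS interim analysis and the power table are unaffected, and OS is one of several measures in a secondary item. This should be fixed. Confidence is moderate, because the documents that could show survival follow-up are not available.

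**What to change.** Reconcile Assessments on study and Collection of clinical data with Study design, ICI treatment and Secondary outcome measures, as follows:

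1. State that vital status and date of death, or date last known alive, are collected from routine records for all patients in cohorts 1–6 until study closure, regardless of progression. Exempt this item explicitly from the stopping point in both scheduling sections.
2. State that OS is censored only at the date last known alive.
3. If Additional file 3 or the full protocol already provides for this, correct the two scheduling sections to agree with it.

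The cost is one extra eCRF item at the existing 6-monthly points after progression. It needs no extra visit, sample or procedure, which fits the article's statement that no clinic visits beyond standard of care are required.

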### Biological sample collection

A stool sample, oral swab sample, blood samples and routine laboratory data (as per local practice) will be collected at baseline (pre-treatment).

Further stool samples will be collected at approximately 3–6 weeks (ahead of the 6–8 week visit), 9–12 weeks (ahead of the 12 week visit), approx. 6 months, at the time of a CTCAE grade > 3 IrAE, at disease progression, relapse or at 1 year, whichever occurs soonest.

Further blood samples will be taken at a clinic visit approximating to 12 weeks, at 1 year or on progression/relapse, whichever is sooner, and at the time of documenting a significant (CTCAE grade > 3) IrAE.

Patients are asked to consent to allow access to any available archival tumour tissue previously obtained, as well as any excess tumour tissue acquired during the study period (as per local practice).

Patients will also be asked for permission to access any biopsies taken from planned surgery as part of their treatment, including an organ(s) affected by toxicity (e.g. liver or skin biopsy) during the course of this study, to be used for this research.

Registered household controls will be invited to attend a convenient clinic visit with the patient to provide relevant information, have a blood sample taken and receive a stool and oral swab sample collection kit.

### Sample size

No established power and sample size calculations exist for studies where the final analyses are of the nature necessitated in this project. We follow the broad approach of simulation-based power calculations. In particular, we used data based on the microbiome samples taken from the patients of the pilot study to populate the corresponding probabilities of a Dirichlet-multinomial model. These probabilities were then used to simulate 1000 cohorts of 10,000 responders (individuals with progression free survival) and 10,000 non-responders, i.e. those with progression or death. We then used the proportions of being alive and progression free or not for each of the first six cohorts and calculated how well the model would estimate the corresponding probabilities in order to estimate the power for a range of sample sizes. Table 3 gives the estimated power for three indicative cohorts and for different sample sizes. These are looking at groups of advanced melanoma patients treated with nivolumab and nivolumab+ipilimumab, where the probability of PFS after 12 months was estimated at 42 and 50% for the two cohorts respectively. The third is based on a cohort of advanced NSCLC patients treated with pembrolizumab with a 47% probability of PFS after 12 months [30].

**Table 3 Tab3:** Estimated power based on cohort and sample size

	100	150	200	300	400	600
Melanoma Nivo 1 year PFS	0.650	0.682	0.710	0.738	0.754	0.759
Melanoma Nivo+IPI 1 year PFS	0.754	0.766	0.775	0.784	0.788	0.795
NSCLC Pembrolizumab 1 year PFS	0.732	0.750	0.764	0.776	0.782	0.790

It is apparent that, as expected, the power increases with the sample size, but at a slower rate. A number of approximations are used behind these calculations, with the main one relating to the lack of detailed data on the gut microbiome signature for the melanoma patients and a complete lack of data for lung and renal cancer patients. Therefore, we propose to use a minimum of 50 patients for each of the first six cohorts and re-evaluate the sample size calculations once more data become available on the gut microbiome profile. This calculation will be done when at least 50 patients from each cohort have given samples and taxonomic metagenomics and culturing methods can be applied to update the current evidence on the ability of the microbiome signature to detect the probability of responding to treatment or not.

### Statistical analysis methods

The main clinical outcome to be correlated with the gut microbiome metagenomic data will be PFS in patients with advanced disease. The hypothesis to be tested is concerned with the effect of the microbiome profile on PFS. There will be an interim analysis evaluating the effect of the biomarkers on 6-month PFS while the main analysis will assess the effect on 1 year PFS.

All primary analyses will be based upon a regularised logistic regression with the false discovery rate being controlled at 0.05 and the regularisation parameter being estimated using cross-validation.

Two sensitivity/exploratory analyses will be conducted to assess the robustness of the composition of the microbiome signature and its exact effect on the clinical outcome. The first will estimate the effect of the biomarkers on the complete survival curve (up to the particular follow-up) using a Cox model. The second will use a random forest classifier to evaluate the effect of the microbiome profile on the PFS.

Regularised logistic regression will be also used for associating the gut microbiome with a number of secondary endpoints, such as the incidence of adverse events. The secondary outcomes which depend upon the complete survival curve such the median PFS and the median OS will be correlated to the microbiome signature using a Cox model.

The logistic regression and Cox model-based analyses are likely to be conducted in R using the glmnet package. The random forest classifier will likely be fitted using the random Forest R package. A detailed statistical analysis plan will be produced before the final data base lock or before any interim analysis is performed (as appropriate).

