### Study objectives

#### Primary objective

The primary objective is to assess whether there is a gut microbiome ‘signature’ which can predict for ICI treatment efficacy in patients with advanced, unresectable cancers.

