### Study outcome measures

#### Primary outcome measure

Based on pilot data and using an iterative process, a putative microbiome signature was defined [27] and will be prospectively evaluated for its ability to stratify cancer patients receiving ICIs into treatment responders and non-responders. The primary outcome measure is the ability to predict for progression-free survival (PFS) of > 1 year. The primary outcome will be determined for an initial series of patient cohorts limited to advanced melanoma, renal cancer and non-small cell lung cancer (NSCLC) (Table 1 and Fig. 2).

**Table 1 Tab1:** Cohorts 1–6 – Advanced disease cohorts and defined standard of care ICI-containing treatment regimens

Cohort	Disease	Regimens	Primary outcome measure
Cohort 1	Unresectable AJCC stage 3 or 4 melanoma	Anti-PD-1 monotherapy (nivolumab or pembrolizumab)	1 year PFS
Cohort 2	Unresectable AJCC stage 3 or 4 melanoma	Ipilimumab+nivolumab	1 year PFS
Cohort 3	Advanced renal cell carcinoma	Anti-PD-(L)1 + kinase inhibitor	1 year PFS
Cohort 4	Advanced renal cell carcinoma	Ipilimumab+nivolumab	1 year PFS
Cohort 5	Advanced NSCLC	Anti-PD-(L)1 monotherapy in the first-line setting	1 year PFS
Cohort 6	Advanced NSCLC	Anti-PD-(L)1 + chemotherapy ± antiangiogenic in the first-line setting	1 year PFS

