### Interim analysis

In the first stage of this study, a total of 50 patients will be recruited in each of the first 6 cohorts with specific types of advanced cancer: melanoma, renal cancer and NSCLC and followed for a minimum of 6 months. The outcomes of this first stage will determine on-going enrolment and any requirement to amend the protocol.

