## Discussion

ICIs are revolutionising cancer management, with growing evidence of activity across a wide spectrum of cancers. However, generally the minority of patients treated with these high-cost drugs benefit, while IrAEs can be devastating. There is an urgent need to identify biomarkers that are predictive of treatment response, resistance and toxicity, and emerging data points to the gut microbiome as an important influencer of these outcomes [7, 11].

So far, identification of specific responsible bacterial taxa has been inconsistent between published studies, which likely reflects small patient cohorts studied, as well as limitations in analytical methodologies used. By culturing and metagenomic sequencing stool sample bacteria, our group has identified a unique consortium of bacteria, which appears to be predictive of response to ICIs across all key published series as well as our own melanoma patient series [27].

MITRE is a large-scale, multicentre study on the NIHR portfolio, which will generate the largest cancer microbiome dataset of its kind. The main objective of the MITRE study is to prospectively evaluate and validate a gut microbiome ‘signature’ which can predict ICI efficacy in patients with advanced cancer, as well as its role for predicting severe ICI-induced toxicity. Collection of associated blood and tissue samples will provide a rich resource with which to interrogate immune and genomic factors that may explain the functional interplay of the microbiome and our immune system.

A number of clinical studies have demonstrated that therapeutic microbiome manipulations can be used to treat infections and autoimmune diseases; and going forward this approach may be feasible for cancer patients receiving immunotherapy. Indeed recently, as proof of principle, transplant of faecal microbiota was recently shown to promote response in a small number of ICI- refractory melanoma patients [23]. Outcomes from the MITRE study can be expected to inform future strategies for manipulating the patient microbiome with a view to enhancing treatment efficacy in the future.

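### The primary analysis, as described, re-estimates a microbiome signature in MITRE patients and does not test the pre-defined signature named in the primary outcome

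*Protocol article*

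**What the plan says.** Under Primary outcome measure, the protocol article says that, from pilot data, "a putative microbiome signature was defined [27] and will be prospectively evaluated for its ability to stratify cancer patients receiving ICIs". It continues: "The primary outcome measure is the ability to predict for progression-free survival (PFS) of > 1 year", for the six advanced-disease cohorts. The Abstract gives the same primary outcome in terms of the signature. The Discussion states the main objective as to "prospectively evaluate and validate a gut microbiome ‘signature’ which can predict ICI efficacy in patients with advanced cancer".

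Under Statistical analysis methods, the hypothesis concerns the microbiome profile, and "All primary analyses will be based upon a regularised logistic regression with the false discovery rate being controlled at 0.05". The same sentence names cross-validation as the way to choose the regularisation parameter. Two further analyses, a Cox model and a random forest, are to "assess the robustness of the composition of the microbiome signature and its exact effect on the clinical outcome".

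Other sections are looser. The formal objective reads: "The primary objective is to assess whether there is a gut microbiome ‘signature’ which can predict for ICI treatment efficacy". The Rationale and the Abstract's background both pair exploring with validating. Median PFS and median OS, which are secondary, are to be related to the signature by a Cox model. A detailed analysis plan is promised before any interim analysis or final lock.

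On staging, 50 patients in each of the six cohorts are followed for at least 6 months, and "The outcomes of this first stage will determine on-going enrolment and any requirement to amend the protocol". The Sample size section uses these patients to update the evidence on the signature.

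**The concern.** Evaluating a signature that already exists and building one from the data at hand are different tasks. Evaluation takes a fixed rule, applies it to patients who played no part in making it, and reports how well it separates outcomes. Building estimates many coefficients from those outcomes, which is why it needs a penalty and control over many hypotheses. The outcome section promises the first and the analysis section describes the second.

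The validation claim is at stake. A model fitted and judged in the same patients can look predictive when it is not. Meanwhile the pilot signature, for which MITRE offers fresh patients, would have no primary test of its own.

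**Working it through.** **1. The sections side by side.**

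| Element | Primary outcome measure | Statistical analysis methods |
|---|---|---|
| Predictor | Signature already defined on pilot data | Microbiome profile; entering predictors not listed |
| Weights | Nothing to estimate if the signature is fixed | Estimated under a tuned penalty |
| Hypotheses | One per cohort for a fixed score | Many, implied by false discovery rate control |
| Composition | Given | Checked for robustness, so treated as a result |
| Performance | Ability to predict PFS beyond 1 year | Cross-validation named for the penalty only |

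A fixed score needs neither a tuned penalty nor false discovery rate control within a cohort. Even if the predictors were restricted to the signature's own taxa, re-estimating their weights would still not test the pilot rule.

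**2. The plan's own figures.** Table 3 cannot be rebuilt, because the Dirichlet-multinomial parameters, effect size and decision rule are not given. As a check, its N = 100 power was scaled as for one ordinary test: power(N) = Φ[(z_power + 1.96)·√(N/100) − 1.96]. All three rows reach about 1.00 at N = 600, against the stated 0.759, 0.795 and 0.790. Table 3 therefore does not behave like power for a single fixed-signature test. It does not show what it is power for.

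**3. Size of same-data optimism (illustrative).** A lasso logistic model with 5-fold cross-validated penalty was fitted, then scored in its own patients and in new ones. Feature counts and effects are assumptions.

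| Setting | n | Mean AUC, own patients | Mean AUC, new patients |
|---|---|---|---|
| No signal, 300 correlated features | 50 | 0.682 | 0.501 |
| No signal, 300 correlated features | 300 | 0.568 | 0.500 |
| No signal, 100 / 300 independent features | 50 | 0.686 / 0.725 | 0.495 / 0.499 |
| No signal, 100 / 300 independent features | 100 | 0.585 / 0.656 | 0.506 / 0.502 |
| No signal, 100 / 300 independent features | 300 | 0.580 / 0.577 | 0.498 / 0.507 |
| 10 true taxa, 0.4 log-odds per SD, 300 features | 50 | 0.659 | 0.516 |
| 10 true taxa, 0.4 log-odds per SD, 300 features | 300 | 0.843 | 0.681 |

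In the independent-feature runs with no signal, a fixed nine-feature score gave 0.497 to 0.519. The correlated-feature runs used 60 to 100 replicates and the independent-feature runs 30 per setting. None applies a false discovery rate step.

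**4. What a locked score could detect.** The Hanley–McNeil variance is [A(1−A) + (n₁−1)(Q₁−A²) + (n₀−1)(Q₂−A²)]/(n₁n₀), with Q₁ = A/(2−A) and Q₂ = 2A²/(1+A). The event split uses the protocol's 47% PFS for NSCLC.

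Example: A = 0.65, n = 200, n₁ = 94, n₀ = 106. Then Q₁ = 0.4815, Q₂ = 0.5121 and A² = 0.4225. The variance is (0.2275 + 93 × 0.0590 + 105 × 0.0896)/9964 = 0.00152, so SE = 0.039. Power at two-sided 0.05 is Φ(0.15/0.039 − 1.96), about 0.97.

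| Assumed AUC | n = 50 | n = 100 | n = 200 |
|---|---|---|---|
| 0.55 | 0.09 | 0.14 | 0.23 |
| 0.60 | 0.24 | 0.42 | 0.70 |
| 0.65 | 0.48 | 0.78 | 0.97 |
| 0.70 | 0.76 | 0.97 | >0.99 |

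These are per cohort, before any multiplicity adjustment. The documents give no AUC, so only the range is informative.

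**The case against.** The other side has several fair points.

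- **Mixed aim.** The formal objective asks whether a signature exists, the Rationale speaks of exploring as well as validating, and the signature is called putative. A penalised model does address that looser question. This stands, but it does not reconcile the analysis with the primary outcome measure.
- **Unstated predictors.** A reader might infer that taxa are certain to be re-selected. The text does not list the predictors or define the false discovery rate family, so this is a strong inference and not a stated fact.
- **Signature tested elsewhere.** A reader might infer that the pilot signature is never tested. The documents do not support that: secondary survival outcomes are related to the signature by Cox model, though it is unclear whether the pilot or a refitted version is meant.
- **Analysis plan to come.** Cut-offs, performance measures and hold-out rules are normal content for that plan, and the article does not say that same-data AUC will be reported. This stands for the details. However, the article itself commits every primary analysis to the penalised regression, so a plan that made a fixed score primary would depart from it.
- **Simulations.** With no true signal anywhere, valid false discovery rate control at 0.05 would allow any discovery in at most about 5% of datasets. The null AUCs therefore describe the penalised fit alone. At n = 50 the own-patient AUC was even lower with signal (0.659) than without (0.682), so it is a noisy measure there.
- **Locking is contestable.** The Sample size section admits having no microbiome data for lung and renal patients. A melanoma-derived score may do poorly in cohorts 3 to 6.

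**Conclusion.** The point holds in a limited form: the primary analysis as described does not test the signature named in the primary outcome. It re-estimates weights, and probably composition, and the cross-validation it names does not yield an unbiased measure of prediction. This rests on comparing the article's own sections and needs no simulated figure.

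The simulations show only the direction and a plausible size of optimism, under assumed feature counts, a lasso penalty and no false discovery rate step. They do not forecast what MITRE would report. Nor is a locked score free of multiplicity: six cohorts remain, and at 50 patients per cohort power is modest unless the AUC is near 0.70.

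The matter is important because it decides whether a claim of validation can be supported.

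**What to change.** Reconcile Primary objective, Primary outcome measure, Statistical analysis methods and Discussion on which signature is the primary predictor. Specifically:

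1. Fix the pilot signature and its scoring in a dated document before any MITRE outcome is linked, including the 6-month interim outcomes.
2. Make the primary analysis a logistic model of 1-year PFS on that score. Report AUC with 95% CI per cohort and pooled, with a stated rule for multiplicity over the six cohorts.
3. Keep the regularised regression as a discovery analysis. Name its candidate predictors and its false discovery rate family, and take its performance from nested cross-validation or from patients not used for fitting.
4. If first-stage patients (6 × 50 = 300) are used to revise the signature, validate the revised version only in later patients.

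The cost is protocol and analysis-plan wording plus analysis work; no new samples are needed. The downsides are real. A revised signature would lose at least 300 patients from its validation set, and a melanoma-derived score may fail in the renal and lung cohorts. Whether the pilot signature already carries weights and a cut-off cannot be seen from the article. If it does not, they must be set from pilot data alone.
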